## Abstract

**Background:**

Fatigue is one of the most prevalent and burdensome symptoms for patients with inflammatory bowel disease (IBD). Although fatigue increases during periods of inflammation, for some patients it persists when disease is in remission. Compared to other long-term conditions where fatigue has been extensively researched, optimal management of fatigue in patients with IBD is unknown and fatigue has rarely been the primary outcome in intervention studies. To date, interventions for the management of IBD-fatigue are sparse, have short-term effects and have not been implemented within the existing health system. There is a need to integrate current best evidence across different conditions, patient experience and clinical expertise in order to develop interventions for IBD-fatigue management that are feasible and effective. Modifying an existing intervention for patients with multiple sclerosis, this study aims to assess the feasibility and initial estimates of efficacy of a cognitive behavioural therapy (CBT) intervention for the management of fatigue in patients with IBD.

**Methods:**

The study will be a two-arm pilot randomised controlled trial. Patients will be recruited from one outpatient IBD clinic and randomised individually to either: Group 1 (CBT manual for the management of fatigue, one 60-min session and seven 30-min telephone/Skype sessions with a therapist over an eight-week period); or Group 2 (fatigue information sheet to use without therapist help). Self-reported IBD-fatigue (Inflammatory Bowel Disease-Fatigue Scale) and IBD-quality of life (United Kingdom Inflammatory Bowel Disease Questionnaire) and self-reported disease activity will be collected at baseline, three, six and 12 months post randomisation. Illness perceptions, daytime sleepiness, anxiety and depression explanatory variables will be collected only at three months post randomisation. Clinical and sociodemographic data will be retrieved from the patients’ medical notes. A nested qualitative study will evaluate patient and therapist experience, and healthcare professionals’ perceptions of the intervention.

**Discussion:**

The study will provide evidence of the feasibility and initial estimates of efficacy of a CBT intervention for the management of fatigue in patients with IBD. Quantitative and qualitative findings from the study will contribute to the development and implementation of a large-scale randomised controlled trial assessing the efficacy of CBT interventions for IBD-fatigue.

**Trial registration:**

ISRCTN Registry, ISRCTN17917944. Registered on 2 September 2016.

**Electronic supplementary material:**

The online version of this article (doi:10.1186/s13063-017-1926-3) contains supplementary material, which is available to authorized users.

## Background

Inflammatory bowel disease (IBD) mainly encompasses two related but distinct conditions of the gastrointestinal tract: ulcerative colitis (UC) and Crohn’s disease (CD). UC is characterised by diffuse mucosal inflammation limited to the rectum and colon. CD is characterised by patchy, transmural inflammation, affecting any part of the gastrointestinal tract from the mouth to the anus [1–3]. IBD is a lifelong condition, which frequently presents in adolescence or young adulthood and follows an unpredictable relapsing and remitting course. The prevalence of IBD in the United Kingdom (UK) is about 300,000 with CD and UC affecting 5–10 and 10–20 new patients, respectively, per 100,000 people per year [4].

Patients with IBD are affected by a number of symptoms, undergo lifelong pharmacological treatment and have an increased risk of malignancy [5, 6]. Due to the severity of IBD, psychological distress is also common [7], with prevalence of symptoms of depression and anxiety around 22% and 35%, respectively [8]. As IBD has an early life onset, a chronic nature and does not generally shorten lifespan, addressing how patients deal with their disease is an important aspect of care [9]. The current standard care in IBD treatment is aimed at managing the inflammatory response during flare episodes and maintaining remission, with an emphasis on adhering to a regular medication regime [10]. However, manifestations of IBD cannot be fully accounted for by pathophysiology and the simple targeting of inflammation does not necessarily reduce the symptoms affecting patients the most [11–13]. In line with the international expert consensus of the recent Therapeutic Targets in Inflammatory Bowel Disease (STRIDE) initiative [14] on treatment targets for IBD, it is therefore important to shift from management of IBD aimed solely at achieving endoscopic remission to also evaluating patient reported outcomes (PROs) with the ultimate goal of improving patients’ quality of life (QoL) [15].

Fatigue is a common and predominant concern for patients with IBD, experienced by 44–86% of patients with active disease and 22–41% of patients in remission [16]. Fatigue is a complex, multifactorial and multidimensional phenomenon, which has been described as a ‘persistent overwhelming sense of tiredness, weakness, or exhaustion’ [17], that can be mental, physical or both [18]. Unlike everyday tiredness, fatigue is often unrelieved by sleep or rest [19], can have a substantial negative impact on patients’ QoL [20–23] and it may limit patients in their everyday lives [24]. Although fatigue understandably increases during periods of inflammation, for some patients it persists when disease is in clinical and endoscopic remission [25].

Despite the pervasiveness of fatigue as a chief complaint in IBD patients [23], it is only identified and treated in a relatively small proportion of those affected [26]. The causes of fatigue in IBD are not well understood by either patients [27] or healthcare professionals (HCPs) [28]. Disease activity [22, 29–31], anaemia [32–34] and inflammation [32] have been found to be predictive of fatigue, yet there is a considerable number of IBD patients with no apparent physiological underpinnings for their fatigue [35]. Apart from a consistent relationship with disease activity, IBD-fatigue has been linked to psychosocial factors such as low mood [31, 36, 37] and sleep problems [29, 31, 37, 38]. However, most previous research has focused on the relationship between fatigue and clinical variables. The ways in which clinical variables and potentially modifiable factors interact with each other in fatigue has rarely been explored [39].

The complex aetiology of fatigue [16], its subjective nature [40] and the lack of objective ‘gold standard’ to measure fatigue [41], also add to the challenge of developing suitable and effective management methods. Optimal management of fatigue in patients with IBD is unknown and fatigue has rarely been the primary outcome in intervention studies [42–45]. Pharmacological trials utilising biologic therapy [46–48], thiamine [43] or ferumoxytol [49] have shown potential benefits for fatigue. However, these are contrasted by findings in observational studies showing higher fatigue in patients taking biologic therapy [23, 30, 31] and it is unclear whether these effects are due to a reduction in inflammation or to a direct influence on fatigue-signalling pathways [50]. Despite the known importance of physical activity in IBD-fatigue [31, 51], the only trial [45] examining the effect of advice to increase physical activity provided inconclusive results. A few psychosocial interventions, such as problem-solving, solution focused therapy (SFT) [42, 44] and stress management [52], have shown promising effects which declined over time and studies included only a small number of participants.

Stress management [52] has been compared with conventional medical treatment in 45 patients with CD. Self-directed stress management significantly reduced tiredness post-treatment, at six-month and 12-month follow-up. However, fatigue was measured with a symptom diary rating devised by the authors and not with a validated fatigue scale for the assessment of fatigue in long-term conditions [41]. Moreover, fatigue was not the primary outcome of the intervention, making the mechanisms of change difficult to assess. The efficacy of SFT on fatigue and QoL was evaluated in 98 patients with quiescent IBD [44]. After the intervention and at three-month and six-month follow-up, the SFT group showed a significantly greater reduction in fatigue and improvement of QoL comparable to the care as usual group. Yet, the effect was not maintained at nine months post intervention. It is therefore important to design interventions with longer-term effect of reducing fatigue (with follow-up assessments of a minimum of 12 months), in order to determine whether positive effects of interventions can be sustained over long periods of time, and if not, establish the reasons for loss of response over time [53].

Compared to IBD, where fatigue has not been well described, understood or managed [16], in other long-term conditions fatigue has been extensively researched. Drawing from evidence on fatigue in other chronic conditions with relapsing and remitting trajectory, such as multiple sclerosis (MS) and rheumatoid arthritis (RA), can help to identify the mechanism in which psychosocial and clinical factors interact with each other and contribute to higher levels of fatigue, and identify types of interventions for fatigue management in IBD patients. A few fatigue treatment protocols based on cognitive-behavioural models [54–56], employed in large-scale randomised controlled trials (RCTs) in inflammatory conditions (e.g. MS, RA) have found promising results in fatigue reduction [57–59]. Although varying across conditions and symptoms, cognitive-behavioural models are based on the premise that symptoms are maintained by maladaptive cognitive and behavioural factors [60]. Initially, primary disease factors, such as inflammation, may trigger symptoms of fatigue. The ways in which people react cognitively, emotionally and behaviourally to their fatigue may perpetuate or worsen the symptoms [54]. Consequently, altering cognitions, emotions and behavioural responses in relation to fatigue through cognitive-behavioural therapy (CBT) may improve clinical and psychosocial outcomes [61, 62].

Van Kessel et al. [57] assessed the efficacy of delivering CBT or relaxation training (RT) to 72 patients with MS and found that the CBT group reported significantly greater reductions in fatigue nine months post intervention compared to the RT group. Thomas et al. [62–64] compared six weekly sessions of group-based CBT with current local practice in 164 patients with MS and found statistically significant differences in fatigue severity in favour of the intervention group four months and one year post intervention. Similarly, in a two-arm, parallel RCT in adults with RA, Hewlett et al. [58] compared six weekly sessions and a consolidation session of group CBT with self-management information in a 1-h didactic group session. At 18 weeks from the intervention start, CBT participants reported better scores than control participants for fatigue impact and perceived fatigue severity.

For people with IBD, CBT has been utilised for a variety of outcomes, including relapse reduction [65] and perceived stress [66]. Six systematic reviews have collectively appraised studies of psychological treatment for IBD [67–72] with encouraging results. In the most recent systematic review and meta-analysis [72] of RCTs comparing psychological therapy with a control intervention or a control treatment (14 studies), a significant difference in depression scores and quality of life with psychological therapy was observed at the end of therapy in patients with quiescent disease. However, beneficial effects were lost at the final point of follow-up. When assessing the effect of individual physiological therapies on quality of life, only CBT had any significant beneficial effect. In a systematic review of 17 studies, Goodhand et al. [68] concluded that CBT was effective for mood disorders and improved QoL in patients with IBD. McCombie et al. [71] and Knowles et al. [70] evaluated studies of the main types of psychological treatment for IBD and found that CBT and its variants most commonly contributed to positive outcomes as compared to other psychotherapies (i.e. psychoeducation and problem-solving therapy). CBT consistently resulted in improved psychological distress, but with modest effects in gastrointestinal symptoms these were not sustained over time. However, these findings have to be interpreted in light of limitations, including: time and travel burden for patients attending face-to-face sessions; and high attrition rates and low compliance issues for online interventions [73, 74].

There is a need to integrate current best evidence across different conditions, patient experience and clinical expertise in order to develop interventions for IBD-fatigue management that are feasible and effective [75]. Balancing the insights from research and practice can maximise the likelihood of interventions being feasible and acceptable, and of treatment addressing important issues to patients while overcoming previously identified limitations [76].

There is evidence from RCT interventions in other long-term conditions [57–59] to suggest that modifying maladaptive cognitions and behaviours through CBT could be a viable option for the management of fatigue. Drawing from interventions in other conditions can enhance the process of development of new evidence-based management strategies in IBD without ‘reinventing the wheel’ [77]. Previous quantitative [78, 79] and qualitative studies [80] and systematic reviews [16, 39] showed similarities between the perceived experience of fatigue between different disease groups. Across conditions, fatigue is closely related to relapse and more active disease [81, 82] and similar physical and psychosocial factors appear to be causing and exacerbating fatigue [80]. Additionally, the findings from our recent study [83] indicate that the ways patients perceive, interpret and react to fatigue symptoms in IBD is largely comparable to patients with MS specifically [84]. Patients who have more negative perceptions of fatigue, higher levels of all-or-nothing and avoidance behaviours have significantly greater fatigue scores compared to those with less negative cognitions and behaviours in relation to their fatigue.

Based on these premises, the CBT intervention developed by Van Kessel and colleagues [57] for MS was chosen as the basis of our intervention study for IBD patients. Iterative work with both patients and HCPs working with patients with IBD was then conducted in order to tailor the intervention to IBD patients’ needs following the guidelines on Patient and Public Involvement (PPI) involvement in healthcare [85, 86]. An initial trial has shown promising results with patients with MS [57], has a strong theoretical grounding in a CBT model [87] and has incorporated a valuable and in-depth mediation analysis of processes of change after the trial [88]. The intervention involved eight weekly sessions of 50 min and covered: an introduction to the CBT model of fatigue; activity scheduling; changing unhelpful cognitions surrounding MS and fatigue; sleep hygiene and restoring sleep–wake cycles; managing negative emotions; and the role of social support. In MS, calculated effect sizes for fatigue from baseline to the end of treatment were 3.03 for the CBT group and 1.83 for the RT group, with clinically significant improvements in fatigue. Furthermore, in our study [83], negative perceptions of fatigue and avoidance behaviours were identified in patients with IBD. In MS patients in the trial [88] these same perceptions of fatigue and avoidance behaviours improved significantly more in the CBT than in the RT group. Changing negative perceptions of fatigue mediated the decrease in severity of fatigue [88]. Content of the intervention is described in more detail in Van Kessel et al. [57].

As a result of the challenges inherent in evaluating complex interventions such as CBT, the UK Medical Research Council (MRC) Framework for the development of complex intervention [89] recommends a stepwise approach, with an early piloting phase prior to the design of a large-scale trial. Pilot studies resemble the main study in many respects [90], they are a smaller version of the main study that test whether its components can all work together [91]. They are a requisite initial step in exploring a novel intervention [92] and resemble the main study in many respects, including an initial assessment of the primary outcome [93]. The pilot phase hence ensures that money is not wasted on an expensive trial which produces a null result due to problems with recruitment, retention or delivery of the intervention [94] and that end results are more applicable to real-world settings. It was therefore decided to conduct a pilot study prior to a definitive full-scale effectiveness RCT.

The MRC guidance for process evaluation of complex interventions [95, 96] advocates the potential value of the qualitative research in health interventions. This is part of the growing call to move away from the inappropriate use of pilot trials as hypothesis testing to a greater emphasis on their descriptive, feasibility potential [97]. RCTs are considered the ‘gold standard’ for providing evidence in decision-making in evidence-based practice [98], yet they have been criticised for not providing sufficient evidence that is useful in practice [99]. After the trial, qualitative approaches can help to explore reasons for the findings, examine the appropriateness of the underlying theory and steer researchers towards interventions more likely to be effective in the future [100]. Furthermore, qualitative process evaluation supports understanding and explanation of the processes involved during the implementation of an intervention and its potential integration in everyday practice [101]. To date, only an estimated 3–8% of trials have incorporated qualitative research components [102]. The current pilot trial will hence include a nested qualitative component, with interviews with the IBD patients, the therapist/s delivering the intervention and HCPs working with patients with IBD. The nested qualitative component will strengthen the findings by evaluating perceptions of the current pilot intervention and ultimately enhance the acceptability of the intervention in a large-scale trial.

Research questions: What is the feasibility of a CBT intervention for the management of fatigue in patients with IBD? What are the initial estimates of efficacy of an intervention for the management of fatigue in patients with IBD?

## Methods and design

This study will assess the feasibility and initial estimates of efficacy of a CBT intervention for the management of fatigue in patients with IBD. The pilot intervention will have the objectives to:Assess the feasibility of recruiting eligible patients;Assess the willingness of participants to be randomised;Evaluate the compliance rates to the intervention (Therapist Sessions and Homework Sheets);Assess withdrawal and dropout rates during the treatment phase;Assess the completion rates of the outcome measures post intervention and at follow-up times;Determine the adequate sample size for definitive full-scale effectiveness RCT;Obtain initial estimates of efficacy on fatigue and QoL in the CBT intervention group compared to the fatigue Information Sheet group;Obtain detailed qualitative feedback from patients, the therapist/s delivering the intervention and HCPs working with patients with IBD on their experience and views of the intervention and areas for improvement in future fatigue interventions.

The pilot trial will not attempt to provide evidence of clinical effectiveness for the CBT intervention in people with IBD. This is in accordance with the recommendations from the National Institute of Healthcare Research (NIHR) guidelines and the Consolidated Standards of Reporting Trials (CONSORT) for the development of pilot studies [91, 103].

### Study design

The study will be a two-arm pilot RCT. Patients will be recruited from the outpatient IBD clinic at a single specialist hospital site and randomised individually, using a 1:1 ratio computerised algorithm. A nested qualitative study will evaluate patient and therapist experience, and HCPs perceptions of the intervention. The study will have a total duration of 22 months with two phases.

### Phase 1: the pilot randomised controlled trial (*n* = 40)

#### Recruitment

A member of the direct care team at the recruitment site will look through electronic and paper medical records, reviewing the inclusion/exclusion criteria, and identify potentially eligible patients attending the IBD outpatient clinic that day. Consecutive potentially eligible patients attending outpatient IBD clinics from January 2017 to June 2017 will be included in the recruitment process. At the end of their appointment a direct member of their care team will ask patients if they would be happy to be approached by a researcher to take part in a research study. If the patient is interested, they will then be directed to the research room. A member of the research team will hand the patients a Patient Information Sheet (PIS) and provide them with a full verbal explanation of the RCT. Patients will be given adequate time to fully comprehend the content of the PIS and will be given the opportunity to ask questions about taking part in the study. Those who indicate a potential interest in the RCT will be screened for full eligibility using the Eligibility Screening Form. If ineligible, the patient will be thanked for their interest, will not be enrolled in the study and no personal details will be recorded.

Eligible patients will then be given at least 48 h to consider their participation in the study and discuss the decision with family, friends and their care team. A member of the research team will then contact them by telephone to answer any additional questions, verify their understanding of what is involved and confirm their interest in study participation. If patients agree to take part in the study, they will be asked to sign the *Patient Consent Forms-RCT* and complete the *Baseline Data A* booklet. A format for written questions for this phase has been developed and piloted with our PPI group to ensure acceptability and ease of understanding of questions to be asked. Participants will be asked to return the signed *Patient Consent Forms-RCT* and the completed questionnaires in the pre-paid stamped addressed envelope provided within seven days of receipt. The returned study documents will be checked for completeness, and the patient will then be entered into the randomisation database for the RCT and told whether they are in Group 1 (CBT manual + therapist support) or Group 2 (Fatigue Information Sheet only). Screening and consenting will continue until the study target sample size (*n* = 40, 20 for each arm) is reached. Hospital consultants will be informed of the patients’ participation in the study via an entry made in the patient’s notes; with patients’ agreement, their General Practitioner (GP) will be informed using *GP Notification Letter*.

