#### Feasibility and acceptability outcomes

Feasibility of recruiting eligible patients will be evaluated by calculating the proportion of those invited to take part in the intervention that were eligible and then were consented into the trial. The willingness of participants to be randomised will be evaluated by calculating the proportion of those who dropped out of the trial after they have been randomised. Refusal, withdrawal and dropout rates from the study and number of sessions with therapist will be recorded. A post-intervention follow-up questionnaire included in *Outcome Data B* booklet will assess compliance rates to the intervention by asking participants about the number of sessions of the manual they read and time per week spent completing tasks in relation to the intervention. The therapist/s will also record how many sessions the participants have completed. Furthermore, in order to assess compliance to the intervention procedures, if participants are willing to do so, they will be asked to provide the research team with the Homework Sheets completed at the end of each session in the manual. The Homework Sheets will be checked for completion in order to assess compliance with the intervention components.

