### Inclusion criteria

Patients who are currently experiencing fatigue (self-reported)Proof of diagnosis of IBD (record of diagnostic endoscopy in patient clinical notes); patients without this test will not be includedAged 18 years and overNo elevated inflammatory markers or other clinical features of active disease

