### Statistics and data analysis

Due to the pilot design of the study a power calculation was not required. Data collected in the pilot study will be used to generate information for sample size calculations for a definitive full-scale effectiveness RCT. Based on similar pilot studies, a sample of 40 patients (20 per arm) was deemed large enough to provide useful information about the aspects that are being assessed for feasibility. It is recognised that the study may not be powered to detect meaningful differences in clinically important endpoints [91].

Patients will be recruited from an IBD outpatient clinic in London, UK, which is representative of the target study population of patients experiencing IBD-fatigue. The sample was based on the same inclusion/exclusion criteria that would be used in a future definitive full-scale effectiveness RCT. At the study site, a total of approximately 100–150 patients attend four IBD outpatient clinics each week. Assuming around 40% recruitment of eligible patients based on our earlier studies recruiting from this population [83], discussions with the clinical team and recruitment rates for intervention for fatigue in MS [57], our target aim of 40 patients should be reached within the six-month baseline data collection period. Taking into account an attrition rate based on prior research [132] of about 20% for each follow-up, we will aim to achieve a minimum sample size of 40 at baseline, in order to suitably assess outcomes at follow-up.

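### Full eligibility is checked only after two expressions of willingness, so the pilot can bound but not estimate uptake among eligible patients

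*Protocol article*

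**What the plan says.** The first objective listed under Methods and design is: "Assess the feasibility of recruiting eligible patients". The Recruitment section then fixes the order of steps:

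1. A care-team member goes through the records, "reviewing the inclusion/exclusion criteria, and identify potentially eligible patients attending the IBD outpatient clinic that day".
2. At the end of the appointment the care team will "ask patients if they would be happy to be approached by a researcher to take part in a research study".
3. Those who agree receive the information sheet and a verbal explanation from a researcher.
4. "Those who indicate a potential interest in the RCT will be screened for full eligibility using the Eligibility Screening Form".
5. "Eligible patients will then be given at least 48 h to consider their participation in the study". A telephone call follows, and then postal return of the consent form and baseline booklet.

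The first inclusion criterion rests on the patient's own report: "Patients who are currently experiencing fatigue (self-reported".

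Feasibility and acceptability outcomes gives the recruitment measure as "calculating the proportion of those invited to take part in the intervention that were eligible and then were consented into the trial", and says that refusal rates will be recorded. It does not say that eligibility will be recorded for people who refuse before screening.

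The plan for reaching 40 patients in six months, under Statistics and data analysis, begins: "Assuming around 40% recruitment of eligible patients based on our earlier studies recruiting from this population".

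**The concern.** Both the first objective and the 40% figure refer to eligible patients. The pathway settles full eligibility only in people who have agreed to see a researcher and then shown interest after the information sheet. A record review cannot reliably establish a self-reported symptom, and no step before the form is described as asking about it. Someone who declines at the clinic, or after reading the sheet, may be a fatigued and otherwise eligible patient who does not want the study, or may have no fatigue at all. A refusal count cannot separate the two.

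At stake is what the pilot can say about willingness among the people the intervention is meant for, and whether it can check its own planning assumption. Fatigue status not asked at the approach cannot be recovered later.

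**Working it through.** **The plan's own figure.** The 40 patients come from no power formula, so the only arithmetic to reproduce is recruitment.
- Eligible patients needed: 40/0.40 = 100.
- Attendances in 26 weeks at 100–150 per week: 26 × 100 = 2,600 to 26 × 150 = 3,900.
- Share of attendances required: 100/3,900 = 2.6% to 100/2,600 = 3.8%, or 100/26 = 3.8 eligible patients a week.

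The target is arithmetically attainable and is not in dispute.

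**Definitions.**
- I = patients invited, taken as everyone the care team asks
- E = truly eligible patients among them
- S = patients confirmed eligible on the screening form
- C = patients who consent

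Consenting patients are all confirmed eligible, so C ≤ S ≤ E ≤ I, and therefore

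C/I ≤ C/E ≤ C/S.

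The quantity wanted is C/E. The pathway yields I, S, C and refusal counts, but not E. Write a = S/E (share of eligible patients who reach screening) and π = E/I (share of those invited who are eligible). Then

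C/S = (C/E)/a and C/I = (C/E) × π.

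The documents give neither a nor π, so both are shown over assumed ranges, with C/E at the protocol's 40%.

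| Assumed a | C/S = 0.40/a |
|---|---|
| 0.9 | 44% |
| 0.8 | 50% |
| 0.6 | 67% |
| 0.5 | 80% |
| 0.4 | 100% |

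| Assumed π | C/I = 0.40 × π |
|---|---|
| 0.8 | 32% |
| 0.6 | 24% |
| 0.5 | 20% |
| 0.4 | 16% |

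The upper ratio equals the true value only if a = 1, and the lower only if π = 1.

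**Why the counts do not settle it.** Take a = 0.8 and π = 0.5 together, with E = 100 and C = 40. Then S = 0.8 × 100 = 80 and I = 100/0.5 = 200. If nobody who is screened proves ineligible, 200 − 80 = 120 people declined before the form. The trial would see I = 200, S = 80 and C = 40. Those counts fit any E from 80 to 200, so they fit any uptake from 40/200 = 20% to 40/80 = 50%. People screened and found ineligible can be removed from the lower denominator, which narrows the interval but does not close it.

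**A condition on the lower bound.** It needs the invited to be counted at the care team's first question. If they are counted only from the information sheet, eligible patients who declined the approach drop out of the denominator, and the ratio need not lie below C/E.

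**The case against.** The strongest reply is that most of what matters is observed.

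- **Refusers after screening are known.** Full eligibility is settled before the main decision stage. Anyone who declines during the 48 hours, at the call, or by not returning the forms is a known eligible refuser. A reader might infer that eligible patients who decline are never identified; the Recruitment section does not support that. The gap is limited to refusals before the form.
- **Records are checked first.** The review against the criteria and the clinic appointment itself may both enrich for fatigue, so π could be high. This stands, but neither step establishes fatigue. For the same reason, the Background's 22–41% prevalence of fatigue in remission should not be substituted for π: the invited patients have already been filtered.
- **The stated measure does not inflate.** A reader might infer that reported uptake will be too high. On its plain reading, the recruitment measure has those invited in the denominator, which understates uptake among eligible patients. Overstatement arises only if confirmed-eligible patients are used instead.
- **Screening load can be projected.** A reader might infer that the definitive trial's workload cannot be derived. Under the same pathway and criteria, it follows from consented per invited patient. Nor do the two scales conflict when each is labelled: at a = 0.8, 40/0.50 = 80 screened-eligible patients are the same people as 80/0.8 = 100 eligible patients. The limit is transfer to clinics with a different fatigue mix, since the pilot has one specialist site.
- **The 40% may itself be conditional on screening.** The article does not say how eligible patients were counted in its sources. This stands, and is a reason to report more than one ratio.
- **This is a condensed article.** A step-by-step screening log may well be in the full protocol, and its absence here is no fault. What the article does fix is the order of steps, in which nothing before the form is described as asking about fatigue. That part of the concern survives.

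**Conclusion.** The point holds in a limited form. With the pathway as described, patients who decline before the screening form have unknown eligibility, so uptake among eligible patients is bounded by consented/invited below and consented/confirmed-eligible above, and is not estimated. At a true 40%, the bounds would read 20% and 50% if half of those invited are eligible and 80% of eligible patients reach screening. Both shares are assumptions, and the interval could be narrower or wider.

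The conclusion rests on three readings: that records do not settle self-reported fatigue, that fatigue is not asked before the form, and that the invited are everyone the care team asks. It affects the first feasibility objective and the check on the 40% figure. It does not touch the randomised comparison. Gauging interest before detailed screening is a defensible choice, so this is a cheap improvement and not a design failure.

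**What to change.** In the Recruitment section, have the care team ask each potentially eligible patient one yes/no question, whether they currently have fatigue, at the moment they ask about being approached. Keep an anonymous tally, split by that answer, of patients asked, declining the approach, declining after the information sheet, screened, eligible and consented.

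Under Feasibility and acceptability outcomes, report three ratios with named denominators:
- consented / potentially eligible patients reporting fatigue, to be compared with the 40% assumption
- consented / invited, with the invited counted from the care team's first question
- consented / confirmed-eligible

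If the question cannot be added, report the last two as bounds and say that uptake among eligible patients lies between them.

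The cost is a few seconds per patient and a tick-sheet. A minimal anonymous item would be recorded before consent, and the ethics approval should cover it. It fits the existing rule that no personal details are kept for ineligible patients. Some misclassification remains, because early refusers are not fully checked on the other criteria, such as recent CBT or planned pregnancy. The new denominator may therefore still include some ineligible patients, which would pull the first ratio slightly low.
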